## Abstract

**Background:**

Low back pain is an important public health problem that is associated with poor quality of life and disability. Among the electrophysical treatments, interferential current (IFC) has not been studied in patients with low back pain in a high-quality randomised controlled trial examining not only pain, but pain mechanisms and function.

**Methods/design:**

A three-arm randomised controlled trial with patient and assessor blinded to the group allocation. One hundred fifty patients with chronic, nonspecific low back pain from outpatient physical therapy clinics in Brazil. The patients will be randomly allocated into 3 groups (IFC 1 kHz, IFC 4 kHz or Placebo IFC). The interferential current will be applied three days per week (30 minutes per session) over four weeks. *Primary outcome*: Pain intensity. *Secondary outcomes*: The pressure pain threshold, global impression of recovery, disability, function, conditioned pain modulation and temporal summation of pain, discomfort caused by the current. All outcomes will be measured at 4 weeks and 4 months after randomisation. The between-group differences will be calculated by using linear mixed models and Tukey’s post-hoc tests.

**Discussion:**

The use of a placebo group and double-blinding assessor and patients strengthen this study. The present study is the first to compare different IFC carrier frequencies in patients with chronic low back pain.

**Trial registration:**

Brazilian Registry of Clinical Trials: http://RBR-8n4hg2

## Background

Low back pain is an important public health issue that directly affects an individual’s quality of life and activities of daily living (ADLs) [1]. Low back pain is also responsible for many absences from work and has high worldwide socioeconomic costs [2]. The prognosis with acute and persistent low back pain is favourable, and the condition improves or resolves in the majority within the first 6 weeks. However, low to moderate pain levels and disability can persist in patients who become chronic [3].

Inefficient endogenous pain control and central sensitivity are important characteristics in patients with low back pain [4]. Prolonged afferent nociceptive impulses may lead to increased excitability of the central sensory neurons and changes in their plasticity that lead to hypersensitivity resulting in an exaggerated response to pain [5]. Increasing evidence supports the clinical significance of the central sensitisation in patients with unexplained chronic pain; therefore, reduction in central sensitisation should be targeted for the treatment of these patients. The use of conservative therapies such as transcutaneous electrical nerve stimulation (TENS) and manual therapy in experimental models suggests that these treatments can reduce the central sensitization in animals and could desensitise the central nervous system (CNS) in humans [6,7].

The treatment of chronic low back pain aims to reduce pain and disability [8]. Exercise is widely prescribed for treating patients with chronic low back pain [9]. However, patients with low back pain may have significant pain that limits their physical capacity, making it difficult to exercise [10]. Therefore, the use of electrophysical agents to decrease pain could enable these patients to participate in an exercise program at an earlier stage of recovery [10]. Among the electrotherapeutical resources, interferential current (IFC) has been studied for the treatment of acute [11] and chronic low back pain [10]. A recent systematic review concluded that when combined with other treatments, such as exercises and massage, IFC demonstrates advantages over placebo and non-treatment control groups in reducing the intensity of pain associated with musculoskeletal disorders [12]. However, little evidence has indicated that the use of IFC alone can reduce the intensity of pain [12], disability or use of analgesics, or improve function in patients with chronic low back pain [10].

Despite various adjustments to the amplitude-modulated frequency (AMF) often used in clinical practice to treat different injury or disease stages, studies have indicated that AMF does not influence hypoalgesia in healthy individuals [13,14], which suggests that the main parameter that should be adjusted is the carrier frequency of the current to affect the pain inhibitory mechanisms [13]. A 2 kHz carrier frequency is often used to strengthen the muscles, and a 4 kHz frequency is used to produce analgesia. However, this conduct is based on therapists’ personal observations, equipment manuals [15] and not on controlled studies. Only one study [16] has compared the effect of the carrier frequencies of the interferential current on the pressure pain threshold in healthy individuals. This study demonstrated that a 1 kHz frequency provides a higher hypoalgesic response compared with 8 kHz or 10 kHz during and after IFC stimulation. However, the evidence on the use of IFC alone for decreasing pain remains insufficient. In addition, chronic low back pain appears to be linked to central sensitisation and a deficiency in the activation of the central pain inhibition mechanisms. Thus, these patients could possibly benefit from the use of IFC to relieve their symptoms. For these reasons, we decided to conduct a prospective randomized controlled study to assess the effects of IFC on pain at rest and during movement, and the disability in patients with chronic low back pain. This study also aims to assess if the use of IFC would reactivate the innate mechanism of conditioned pain modulation and decrease the central hypersensitivity in chronic low back pain patients.

## Methods /design

### Study design

This is a three-arm randomised controlled trial with patient and assessor blinded to the group allocation. Figure 1 provides a flowchart of the study.

**Figure 1 F1:**
[figure not shown]
Flowchart of the study.

### Participants, therapists, centres

Patients seeking physical therapy treatment at the clinic of the Universidade Cidade de São Paulo - UNICID and the Centro de Especialidades Médicas de Guarulhos - CEMEG through medical referral who present nonspecific low back pain for at least 3 months and with a minimum pain intensity of 3 in the 0–10 pain numeric rating scale (NRS-Brazilian-Portuguese version) [17] during the last 7 days will be included in the study. Patients of both genders with ages ranging from 18 to 80 years old will be included. Patients with severe spinal disorders such as fractures, tumours and inflammatory diseases including ankylosing spondylitis; patients with nerve root disorders confirmed by neurological exams (herniated disks and spondylolisthesis with neurological involvement, spinal canal stenosis and others); patients suffering from neurological diseases, severe cardiopulmonary diseases, pregnancy, infection or skin lesions at the current application site, cancer, or changes in sensitivity and allergy in the region of electrode positioning; and patients who require artificial cardiac pacemakers will be excluded.

Participants will be assessed by the researcher responsible for the assessments during the study to verify that they fit the inclusion criteria. If eligible, they will be informed of the study objectives. They will then sign an informed consent form to participate in the study. The present study was approved by the Research Ethics Committees of Universidade Cidade de São Paulo and Centro de Especialidades Médicas de Guarulhos.

Due to the nature of the intervention, only the therapist responsible for application of IFC will be aware about group allocation; the assessor and the participants will be blinded to the group allocation. To keep the evaluator blind to the study groups, the device will be covered with a dark cloth.

### Intervention

Each participant will be randomly allocated to one of 3 groups: Group IFC 1 kHz (n = 50), Group IFC 4 kHz (n = 50) and a Placebo IFC Group (n = 50). All participants will receive 30 minutes of current stimulation (the current amplitude will not be increased for the participants in the placebo group) 3 times per week on alternate days for 4 weeks for a total of 12 sessions.

The present study will use the Neurovector equipment that produces a medium-frequency alternating current (Neurovector, Indústria Brasileira de Equipamentos Médicos - IBRAMED®, Amparo, Brazil). This equipment was developed exclusively for the present study and is not commercially available. The technique used will involve a bipolar mode with 2 channels located 5 cm from the L3 and L5 spinous processes. The following parameters will be employed: current carrier frequency according to the patient group (1 or 4 kHz); AMF = 100 Hz; Sweep = 50 Hz; 1:1 swing pattern and 30 minutes of stimulation.

The procedures for the placebo group will be similar to those of the other groups; however, the current amplitude will not be increased. The patients will be informed that they may or may not feel any sensation at the application site of the electrodes [13]. For the active groups, the therapist will increase the current amplitude until the participant reports feeling a strong but comfortable tingling. Every 5 minutes, the therapist will ask each participant whether the “strong but comfortable tingling” remains. In case of sensory habituation, the current amplitude will be increased until the participant reaches the previous sensation. After ending the application, the patient will wait for 20 minutes for the necessary measurements be taken.

### Outcome measures

#### Primary outcome

Pain intensity after all treatment sessions and 4 months after randomisation.

#### Secondary outcomes

(1) pressure pain threshold; (2) current discomfort; (3) disability; (4) global impression of recovery; (5) functional performance; (6) conditioned pain modulation and pain temporal summation; and (7) analgesic use measured in all time-points.

### Measurement instruments

#### Pain numerical rating scale (NRS)

Pain intensity will be assessed using the pain numerical rating scale (NRS) [18], which assesses the level of pain intensity perceived by the patient through an 11-point scale (ranging from 0 to 10), with 0 indicating “no pain” and 10 indicating the “worst possible pain”. The pain assessment will be carried out verbally with the patient reporting the pain intensity. This instrument has been translated and cross-culturally adapted for the Brazilian population [17].

The pain will be assessed prior to applying the current, at 30 minutes of treatment with the current still on and 20 minutes after the current is turned off. This variable will be measured in all sessions, after treatment and in the follow-up examination after 4 months.

#### Pressure pain threshold (PPT)

The pressure pain threshold (PPT) will be measured using a Somedic digital pressure algometer (Somedic Inc., Hörby, Sweden). Assessments will be performed prior to application of the current, immediately after the 30^th^ minute of stimulation and 20 minutes after the session has ended. This assessment will be performed in the first and last sessions.

Hygienisation with soap and water will be performed at the assessed sites. After cleaning the skin, the areas to which the algometer will be attached will be marked with a tape measure and a pen. Two points will be marked bilaterally: the first located 5 cm lateral to the L3 spinous process [19] and the second located 5 cm lateral to the L5 spinous process [20]. A point, to be used as a control, will also be marked on the tibialis anterior muscle of the right leg, 5 cm lateral to the tibial tuberosity [21].

The assessor will conduct a preliminary study of intra-observer reliability for measuring the pressure pain threshold at the evaluation points that will be used in the study. Ten participants with chronic low back pain will be recruited and assessed on two occasions that are 48 hours apart. The intra-evaluator reliability for the measurement of the PPT will be estimated by calculating the intraclass correlation coefficients (ICC type 3,2) for the tibialis anterior muscle and the low back muscles.

During the PPT measurements, the circular probe of the algometer (1-cm^2^ area) will be positioned perpendicular to the skin and pressed at approximately 50 kPa/s [22]. Participants will be asked to press a button when the pressure or discomfort sensation becomes clearly painful. Two pressure measurements (in kPa) will be collected from each area at 30-s intervals.

Two demonstrations of the procedure will be conducted for each participant in the extensor muscles of the dominant forearm to ensure that the test is well-understood. The mean values will be used for the lumbar region and the tibialis anterior muscle in the pain threshold data analysis.

#### Current discomfort

The discomfort caused by the current will be assessed using a 10-cm visual analogue scale (VAS) where the far left end indicate “very comfortable” and the far right end indicate “very uncomfortable” [23]. The discomfort will be assessed at 30 minutes of stimulation in all sessions.

#### Roland-Morris disability questionnaire

Disability will be assessed by the Roland-Morris disability questionnaire, which is widely used to assess the functional performance associated with low back pain [24]. This instrument, which has been translated and cross-culturally adapted for the Brazilian population [25], consists of 24 items that describe the daily activities that prove difficult for the patients to perform due to low back pain. Many of the selected items are directly correlated to a greater impairment in functional performance. The patients will be instructed to verbally state which items describe them on the particular assessment day. The questionnaire will be applied on the first and last days of treatment and at the 4-month follow-up (conducted by telephone).

#### Global perceived effect scale

The global impression of recovery will be assessed through the global perceived effect scale [26,27], which has been translated and cross-culturally adapted into Brazilian-Portuguese [17] and corresponds to an 11-point scale ranging from −5 points (much worse) to 0 (no change) to 5 points (completely recovered). To measure the global impression of recovery, the participants will be asked the following: “Compared with the beginning of the first episode, how would you currently describe your back?” Positive scores represent recovery, and negative scores indicate a worsening of the symptoms. The scale will be applied before and after treatment and at the 4-month telephone follow-up.

#### Sit-to-stand test

Functional performance will be assessed through a sit-to-stand test. The patients will be instructed to sit and stand 5 times from a chair with a backrest with their arms crossed in front of them as quickly as they can [28]. The test will be timed, and immediately after the test, the patients will be questioned regarding the low back pain experienced during the test. The test will be performed during the first and last sessions prior to the application of the current and after 30 minutes of current stimulation.

#### Pain temporal summation

Temporal summation (TS) will be induced by an analogue pressure algometer (FPK20, Wagner Instruments, Greenwich, CT, USA) with a circular metal tip measuring 0.79 cm^2^. The evaluator will be trained prior to the data collection. The area selected for TS analysis will be the site indicated as the lower pain threshold in the low back algometry in which three stimuli per second will be applied with a pressure of approximately 2 kg/s to determine the best value for use in the TS test. Next, 10 stimuli will be performed using the algometer on the selected region. Each TS stimulus will be maintained for 1 second before being released, and the stimuli will be spaced at 1-second intervals. A timer will be used to ensure that the intervals are respected and that the stimuli are maintained. Participants will be instructed to report pain using the NRS, which will be posted on the wall in front of them, at the first, fifth and tenth stimulus [29]. The TS assessment will be performed prior to initiating the treatment protocol and prior to current application during the last session. To prevent sensitisation interference from the previously performed pain pressure threshold assessment, the TS assessment will begin 2 minutes after the PPT assessment.

#### Conditioned pain modulation

A cold pressor test will be used to assess the activation of the conditioned pain modulation (CPM) [30]. The conditioned stimulus will involve the immersion of the lower limb on the ipsilateral side of the more painful lumbar region. In cases of bilateral pain, the subject will be instructed to report the most painful side [31]. If no consensus can be reached regarding the most painful side, the right leg will be used. The limb will be immersed in a bucket containing water and ice at 4°C, 3 cm above the lateral malleolus of the ankle. The low back pain intensity will be assessed after 20 seconds of immersion using the NRS. The PPT at the low-back algometry points will be recorded 30 seconds after immersion. After removing the limb from the water, the participants will be questioned regarding their foot pain according to the NRS. A CPM activation test will be performed on the first day of treatment prior to initiating the stimulation and on the last day of the session prior to applying the current so that no interference occurs in the CPM assessment immediately after stimulation.

#### Analgesic use

To assess the use of analgesics during the treatment, the assessor will complete a record listing the days of the week from the beginning of the treatment until the date of the last session to note the use of analgesics or anti-inflammatory drugs and their dosage during treatment [10]. With this information, any reduction in the use of medications during treatment can be assessed.

### Procedure

#### Randomisation

After assessment, the patients will be referred to the therapist responsible for the treatment, who will open the sealed envelope prior to initiating the treatment to determine in which group the patient will be included (Group IFC 1 kHz, Group IFC 4 kHz or the IFC Placebo Group). The randomisation of groups will be performed using a computer-generated, random-number list compiled by an investigator not involved in the patient recruitment or data collection. The group allocation will be concealed by printing the group allocation onto cards and sealing them in consecutively numbered opaque envelopes. The envelopes will be stored in a secure cabinet accessibly only to the allocation investigator and will be opened immediately prior to the intervention allocation.

#### Study-blinding assessment

Following the treatment and the follow-up assessments, the therapist will ask the assessor if she believes that the patient received interferential current or the placebo. Additionally, the study participants will answer the same questions justifying their answers. The answers to these questions will be recorded and used to measure the effectiveness of the study blinding [32].

#### Data analysis

Data will be double-entered and analysis will be performed by a blinded statistician. All statistical procedures will be conducted following the intention-to-treat principles. Initially, the descriptive statistics will be used for the studied variables. The data normalisation will be analysed through a visual inspection of the histograms. The between-group differences in the measurements of the primary and secondary outcomes will be compared via linear mixed models using the interaction terms “group versus time” with a Tukey’s post-hoc test. For the data analysis, the SPSS (statistical package for social sciences) version 19.0 for Windows and Microsoft Excel 2007 will be used. All tests will be performed assuming a significance level of p < 0.05.

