#### Sample size calculation

To obtain the total number of participants in the present study, the sample size was calculated to detect a difference of 1 point in the pain intensity outcome as measured by the numerical rating scale (NRS) (Costa et al. 2008) with a standard deviation of 1.47 points [33]. A statistical power of 80%, a 5% alpha and a possible sample loss of up to 15% were considered. Therefore, 50 patients per group (150 in total) will be required (Minitab, v. 15, State College, PA).

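### The group-by-time model gives baseline pain no stated role; adjusting for it would be at least as precise on either reading of the contrast, at the cost of one degree of freedom

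*Protocol article*

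**What the plan says.** The Data analysis section applies one model to every primary and secondary outcome: between-group differences "will be compared via linear mixed models using the interaction terms" of group and time, followed by Tukey's test. It names no covariate and does not say which occasions make up the time factor.

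The Primary outcome section reads "Pain intensity after all treatment sessions and 4 months after randomisation". On collection, the NRS section says "The pain will be assessed prior to applying the current" and "This variable will be measured in all sessions, after treatment and in the follow-up examination after 4 months". Entry also requires low back pain "with a minimum pain intensity of 3" on the NRS over the last 7 days. A pre-treatment pain score is therefore planned for every patient.

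In the Sample size calculation, "the sample size was calculated to detect a difference of 1 point in the pain intensity outcome" "with a standard deviation of 1.47 points". It continues "A statistical power of 80%, a 5% alpha", allows for 15% loss, and arrives at 50 per group. It does not say whether 1.47 is the SD of a score or of a change, and it uses no baseline correlation.

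**The concern.** In a randomised trial the true baseline means are equal across arms. A model that estimates a separate baseline mean for each arm and measures the effect from it spends information on differences known to be chance. A model that ignores baseline discards a predictor of the outcome. Either way the confidence intervals for the primary outcome are likely to be wider than the collected data allow. The sample size has little slack, so the choice could decide whether a true 1-point difference is detected.

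**Working it through.** **1. The plan's own figure.** A one-way ANOVA with three groups, largest difference 1, SD 1.47 and alpha 0.05 has noncentrality n × 1² / (2 × 1.47²). At n = 43 this is 9.95 and power is 80.3%. Allowing for 15% loss gives 43/0.85 = 50.6 or 43 × 1.15 = 49.5, so the stated 50 per group reproduces to within a patient. No baseline correlation enters.

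**2. Which contrast the model tests.** Without a baseline level, the interaction would test only whether the group difference varies among post-baseline times, and it would miss a constant benefit. The natural reading therefore makes baseline a level of time, and the effect is a difference in change. If Tukey instead compares groups at each time, the effect is a plain follow-up difference.

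**3. Variances.** Let s be the follow-up SD, k the ratio of baseline SD to follow-up SD, and r the correlation of baseline with follow-up. In units of s² × (2/n), with complete data:
- change: 1 + k² − 2rk, which is 2(1 − r) when k = 1
- unadjusted follow-up: 1
- baseline-adjusted: 1 − r²

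Change minus adjusted is (k − r)², which is never negative. Follow-up minus adjusted is r², also never negative. Adjustment is therefore at least as precise under both readings, apart from the one degree of freedom it uses.

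**4. Power for one pairwise comparison.** Inputs from the article: difference 1, SD 1.47, 50 per group less 15% (42.5, taken as 42). Assumptions: 1.47 is the SD of a score, k = 1, and r as shown. The Tukey critical value for 3 groups and 3 × 41 = 123 degrees of freedom is 2.372; power is from the noncentral t.

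| r | Variance, change | Variance, adjusted | Ratio | SE, change | SE, adjusted | Power, change | Power, adjusted |
|---|---|---|---|---|---|---|---|
| 0.3 | 1.40 | 0.91 | 1.54 | 0.380 | 0.306 | 60% | 81% |
| 0.5 | 1.00 | 0.75 | 1.33 | 0.321 | 0.278 | 77% | 89% |
| 0.7 | 0.60 | 0.51 | 1.18 | 0.248 | 0.229 | 95% | 98% |

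The unadjusted follow-up comparison has SE 1.47 × √(2/42) = 0.321 and power 77% at any r. A simulation of 8,000 trials gave SEs of 0.379 and 0.310 at r = 0.3, 0.323 and 0.279 at r = 0.5, and 0.247 and 0.229 at r = 0.7 (change, adjusted). All estimators were centred on the true value.

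**5. What belongs to Tukey.** At r = 0.5 and k = 1 the change SD equals the planning SD, 1.47. Power at an unadjusted two-sided 5% is then 88%; with the Tukey value it is 77%. That fall is due to the multiplicity correction, not to how baseline is handled.

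**6. Unequal SDs.** The entry threshold of 3 may narrow the spread at baseline. With k = 0.7 (an assumption), the change variance is 1.49 − 1.4r:
- r = 0.3: 1.07, ratio to adjusted 1.18, power 74% against 81%
- r = 0.5: 0.79, ratio 1.05, power 87% against 89%
- r = 0.7: 0.51, ratio 1.00, power 98% for both, because k = r

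**The case against.** The strongest reply is that the article never places baseline among the responses and never rules out a covariate, and that a condensed article may leave the time levels to a fuller plan. That stands as far as it goes: the difference-in-change reading is an inference. But the article does name the model and the term that carries the treatment effect, and adjustment is no worse under either reading.

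A second reply is that the low power figures need several conditions at once: baseline in the response, a score SD of 1.47, similar SDs at both times, low r, and the Tukey value. This also stands. If 1.47 is already the SD of a change, the planning SD matches a change contrast and baseline handling creates no shortfall against the plan.

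A reader might infer that the planned analysis is biased or invalid, or that the trial will miss its 80% power because baseline is mishandled. The documents support neither. Under randomisation a group-by-time mixed model gives unbiased estimates and valid tests, and the article gives neither r nor the SD ratio, so no definite shortfall follows from it.

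**Conclusion.** The point holds as a loss of efficiency on the primary outcome. Under the equal-SD, score-SD assumptions, the change contrast has between 1.18 and 1.54 times the variance of the adjusted contrast for r from 0.7 down to 0.3. Against follow-up alone, the saving is a fraction r² of the variance: 9%, 25% and 49% at r = 0.3, 0.5 and 0.7. The gain is small relative to change when r is high or close to the SD ratio, and near zero relative to follow-up alone when r is near zero. The algebra is firm. The size is uncertain, because r, the SD ratio and the meaning of 1.47 are not in the document, and the levels of time are inferred.

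**What to change.** State the levels of the time factor. For each outcome with a pre-treatment value, take only post-baseline values as the response, with baseline value, group, time and group-by-time as fixed effects. The alternative is to keep baseline in the response and constrain its mean to be equal across arms. Report the adjusted pairwise differences at 4 weeks and 4 months with 95% confidence intervals, and say in the sample size section whether 1.47 refers to a score or a change.

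The cost is a sentence or so of text and one degree of freedom. No further patients or measurements are needed.
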